## Outcomes to be measured

Throughout the different phases of this project we aim to explore the following outcomes:

- Phase 1 – The primary outcome is the prescription of OAC drugs including; vitamin K antagonists (VKAs) (acenocoumarol, phenindione or warfarin), or non-vitamin K oral anticoagulants (NOACs) (dabigatran, rivaroxaban, apixaban, or edoxaban).
- Phase 2 - The primary outcome is ischaemic stroke and other thromboembolic events, or the occurrence of major bleeding (MB) defined according to the International Society on Thrombosis and Haemostasis (ISTH) criteria as (1) clinically overt bleeding accompanied by a drop-in haemoglobin level of least 2 g/dl and/or (2) transfusion of at least 2 units of packed red cells, occurring at a critical site (i.e., intracranial, intraspinal, intraocular, pericardial, intra-articular, intramuscular, and retroperitoneal) and/or (3) fatal bleeding. Secondary outcomes will include clinically relevant non major bleeding (CRNMB) that did not satisfy the ISTH criteria and led to hospitalization, medical or surgical treatment, or led to discontinuation of OACs.
- Phase 3 – The primary outcomes include the reoccurrence of MB events or CRNMB for patients who did or did not continue on OACs, the rate of stroke and other thromboembolic events, cardiovascular related mortality, and all-cause mortality. The secondary outcome is the prescription of any OACs after the occurrence of the MB events. We aim to explore the timing of reinitiating OACs from the indexed MB event and whether patients have continued the same OAC before the index haemorrhage event, were switched to another OACs or received lone antiplatelet therapy.

All outcomes will be identified over the course of follow-up through the identification of corresponding Read/SNOWMED codes in patients' electronic health records. Hospitalization secondary to stroke or bleeding are to be identified through linkage to HES APC using the 10th revision of the International Classification of Diseases (ICD-10). ONS mortality data will be used to ascertain specific causes of death (i.e. bleeding related, cardiovascular, or all-cause death) according to ICD-10 codes.

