### **Sample size considerations**

Due to the comparative nature of the second phase of this study, a sample size calculation was undertaken to provide an estimate of the number of cases needed for the second phase of this project (the comparative cohort), and to detect a difference in the major outcomes of interest (ischemic stroke, mortality, or bleeding) between OACs exposed and not exposed NVAF patients. Power calculations were based on stroke within a year of NVAF diagnosis since it is our primary outcome of interest. An Earlier study showed a yearly stroke incidence ranging of 8% with no OACs and 2.8% in patients treated with warfarin. We have assumed an alpha level (two-tailed) of 0.05, a beta of 0.2 (80% power), and a ratio of 5:1 for the OACs exposed-to-unexposed ratios in the matched cohort to detect a relative risk of 2.8 for the dichotomous endpoint (i.e. stroke). This would require a minimum sample number of 970 of patients in OACs treated patients and 194 patients in OACs unexposed patients, giving a total of 1164 patients. Thus, we estimate to have many times the needed numbers in the two databases.

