### **Planned use of linked data and benefit to patients in England and Wales**

For the current study, data linkages to the Hospital Episode Statistic (HES), Office for National Statistics (ONS) death registration data and index of multiple deprivation (IMD) will be required. As the included patients for particular phases will be those eligible for data linkage, then that population will be based on English practices consented to the CPRD linkage scheme. Access to the HES and ONS Mortality data are important aims as we plan to assess the association between patients' outcomes (bleeding events, stroke, and mortality) and OACs prescribing status in NVAF patients. All outcomes will be identified over the course of follow-up through relevant Read/SNOMED codes in patients' electronic records. Stroke or bleeding events will be identified through Read/SNOMED codes in patients primary care records and through linkage to inpatient HES ICD-10 codes in case of hospitalization secondary to stroke or bleeding. ONS data will be used to ascertain specific causes of death (i.e. bleeding related, cardiovascular, or all-cause death), according to ICD-10 codes. While both practice and patient level IMD data will be used to describe OACs prescribing status in terms of level of social deprivation (IMD quintiles), and as covariates in the regression models to be tested across all three phases. By using linked database that include access to longitudinal information on diagnoses, symptoms, laboratory tests, and mortality records, we will be able to thoroughly explore and compare the different outcomes associated with prescribing OACs in NVAF patients. Such information would help to inform guidelines and optimise treatment decisions of OACs for patient with NVAF.

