### Outcomes:

The primary outcome is the composite of ischaemic stroke and other thromboembolic events, or the occurrence of MB events defined according to the ISTH criteria (described in detail in Section D). Secondary outcomes will include CRNMB events that did not satisfy the ISTH criteria and led to hospitalization, medical or surgical treatment, or led to discontinuation of OACs. All outcomes will be identified over the course of follow-up through the identification of corresponding Read codes in patients’ records. For bleeding events since CPRD does not state the number of transfused blood units, any need for blood transfusion along with a Read code for bleeding will be classified as a MB event. Stroke or bleeding events will be identified through Read codes in patients primary care records and through linkage to inpatient HES ICD-10 codes in case of hospitalization secondary to stroke or bleeding. ONS mortality data will be used to ascertain specific causes of death (i.e. bleeding related, cardiovascular, or all-cause death) according

ICD-10 codes. All codes relevant to these outcomes are listed in Appendix 3.

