2. Phase 2 – Comparative study: For comparison of demographic variables and comorbidities among OACs treated and not treated individuals, independent sample t tests will be used for numeric variables, while Chi squared  $\chi^2$  tests or Fisher exact tests will be used for categorical variables. To control for imbalances in patient characteristics between cohorts, we will calculate an exposure-specific propensity score as the predicted probability of receiving OACs conditional upon individuals baseline covariate (as described in section M) using logistic regression models. Then we will consider applying propensity score matching methods to match each OACs unexposed controls to up to 5 NVAF OACs exposed cases using a calliper of 0.2 standard deviation (SD) of the propensity score logit. After matching, Cox regression will be used to compute hazard ratios (HRs) of the outcomes of interest, comparing exposure to OACs versus no OACs. Initially crude HRs will be obtained, then stratified by type of OACs (i.e., VKAs and NOACs) and adjusted for age, and other important covariates described in section N. In this phase immortal time bias would occur due to the definition of exposure, where in the time from AF diagnosis till receipt of OACs those in the “OACs prescribed group” cannot have the outcome by design, otherwise they would have been classified as non OAC users. To avoid the problem of immortal time bias, we will consider using time-varying exposures, where in a survival analysis, the time period previous to the index date of OACs initiation is reclassified as nonuser for those in the “OACs prescribed group”.

3. Phase 3 – Major bleeding events cohort: At first, we will use descriptive statistics to present the overall characteristics of this cohort who have experienced major bleeding events while taking OACs. After that patients will be divided to 2 groups one for the patients who resumed anticoagulation after the index major bleeding event and the other for the group who remained OACs free and will compare the patient characteristics between the two groups using Chi squared  $\chi^2$  tests, Fisher's exact tests, and analysis of variance, as appropriate. Survival (time-to-event) models will be constructed to compare the time between the indexed major bleeding to the earliest event of stroke, bleeding, or all-cause mortality considering if patients were restarted on OACs or not. In Cox models we will control for age, time to OACs resumption, CHA2DS2-VASc

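### Stroke and thromboembolic deaths known only from the death record are not events in the Phase 2 primary composite or the Phase 3 stroke outcome; a one-sentence rule would capture them.

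*Protocol*

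**What the plan says.** Three places set the sources for stroke: Outcomes to be measured, Planned use of linked data, and the Phase 2 Outcomes paragraph under Exposures, outcomes and covariates. The Phase 2 paragraph reads "Stroke or bleeding events will be identified through Read codes in patients primary care records and through linkage to inpatient HES ICD-10 codes", the inpatient codes applying when the event led to admission. The other two places name the same kinds of source.

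Death registration has a separate task. The linkage section says "ONS data will be used to ascertain specific causes of death (i.e. bleeding related, cardiovascular, or all-cause death", and the Phase 2 paragraph repeats this almost word for word. Neither names stroke or thromboembolism as a cause of death to be ascertained.

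The definition of major bleeding (MB) in Outcomes to be measured ends with a fatal limb, "and/or (3) fatal bleeding". The stroke/thromboembolism outcome has no such limb.

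The Phase 2 paragraph defines the endpoint as follows: "The primary outcome is the composite of ischaemic stroke and other thromboembolic events, or the occurrence of MB events". Cardiovascular death is not a component. In Phase 3, cardiovascular and all-cause mortality are listed as primary outcomes beside the stroke/thromboembolism composite.

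**The concern.** A patient may die of an ischaemic stroke or systemic embolism at home or in a care home, with no admission and no GP stroke code. Under the stated sources that patient has no stroke event. In the Phase 2 Cox model for the primary composite, follow-up ends at death without an event, although the cause of death was the outcome under study. These are the most severe events the outcome is meant to capture, and the ONS data that would identify them have already been requested.

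The protocol aims to weigh stroke prevention against bleeding. It therefore matters that deaths from the two causes be handled by one explicit rule. At present the bleeding definition includes fatal events without saying which source supplies them, and the stroke definition does not mention fatal events.

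**Working it through.** **1. Where a death-record-only thromboembolic death would be counted**

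| Result | Counted as written? | Basis |
|---|---|---|
| Phase 2 primary composite | No | Sources are GP codes and HES admissions; no cardiovascular-death component |
| Phase 2 all-cause mortality | Yes | Named in the Technical Summary, specific aim 4 and Selection of comparison groups |
| Phase 3 stroke/thromboembolism | No | Same event sources in Outcomes to be measured |
| Phase 3 cardiovascular mortality | Yes, if the death is classed as cardiovascular | Phase 3 Outcomes |
| Phase 3 all-cause mortality and the time-to-earliest-event model | Yes | Phase 3 Outcomes; Data/statistical analysis |

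**2. Inputs for size**

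Sample size considerations gives a "yearly stroke incidence ranging of 8% with no OACs and 2.8% in patients treated with warfarin". The stroke ratio, OAC versus none, is 2.8/8 = 0.35. Its inverse is 8/2.8 = 2.86, consistent with the protocol's relative risk of 2.8. The absolute difference is 8 − 2.8 = 5.2 points. The protocol's sample size does not bear on this point.

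The share f of strokes known only from the death record is not in the documents. I assume 5% to 20%.

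**3. Stroke alone, equal loss in both groups**

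Observed ratio = 2.8(1−f) / 8(1−f) = 0.35 for every f. Observed difference = 5.2(1−f):
- f = 5%: 4.94 points
- f = 10%: 4.68 points
- f = 20%: 4.16 points

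**4. Stroke alone, unequal loss**

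The ratio can move either way:
- 10% lost in unexposed, 5% in exposed: 2.66/7.20 = 0.369
- 5% lost in unexposed, 10% in exposed: 2.52/7.60 = 0.332

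The absolute difference shrinks unless 2.8 × f(exposed) exceeds 8 × f(unexposed). That requires the exposed share to be more than 2.86 times the unexposed share.

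**5. Composite, equal loss of strokes, all fatal bleeds counted**

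The protocol gives no MB risks. I assume 1.5% unexposed and 3% exposed, and add stroke and MB risks as if they did not overlap. Ratio = [2.8(1−f) + 3] / [8(1−f) + 1.5]:
- f = 0: 5.80/9.50 = 0.611
- f = 5%: 5.66/9.10 = 0.622
- f = 10%: 5.52/8.70 = 0.634
- f = 20%: 5.24/7.90 = 0.663

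With MB 1% v 2%, the ratio goes from 4.80/9.00 = 0.533 to 4.24/7.40 = 0.573 at f = 20%. With 2% v 4%, it goes from 6.80/10.00 = 0.680 to 6.24/8.40 = 0.743.

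**6. Composite, if ONS bleeding deaths are not counted either**

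If the same share f is lost from MB as from stroke, (1−f) cancels and the composite ratio stays at 0.611. The shift in step 5 therefore depends on a rule that the protocol does not state.

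**The case against.** A reader might infer that fatal bleeds are read from death registration while fatal strokes are not, so that the comparison tilts against OACs. The documents do not support that. The source sentence treats stroke and bleeding alike, and no sentence routes an ONS bleeding death into MB. The link is a plausible inference from the fatal limb together with the ONS bleeding-related category. The Phase 3 index bleed is identified from primary care codes and HES only.

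A reader might also infer that more strokes are lost among untreated patients, because the Study background says the very elderly are less often anticoagulated. That is a crude difference. Phase 2 matches or weights on a propensity score that includes age and comorbidities, and then adjusts for age, frailty and the Charlson index. Differential loss is not shown, so neither is a shift in the stroke hazard ratio.

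Nor are these deaths lost from the study altogether: all-cause mortality keeps them in both phases, and Phase 3 has cardiovascular mortality as well.

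Finally, the protocol says "All codes relevant to these outcomes are listed in Appendix 3", and that appendix is not in the copy at hand. It may contain cause-of-death codes for stroke. But the outcome text assigns the stroke ICD-10 codes to inpatient HES, so a code list alone would not change which source makes an event.

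These objections remove any claim about direction. The gap in the stated source rule remains.

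**Conclusion.** The point holds in a limited form. As written, an ischaemic stroke or systemic embolism known only from the death record is a non-event in the Phase 2 primary composite and in the Phase 3 stroke/thromboembolism outcome. The protocol also leaves unsaid whether ONS bleeding deaths satisfy the fatal limb of MB.

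The size cannot be established from the documents. With equal loss the stroke-only ratio is unaffected and the absolute stroke difference shrinks by exactly the share lost. For an assumed 5% to 20% loss, the composite ratio moves from 0.611 to between 0.622 and 0.663. That range also rests on assumed MB risks of 1.5% v 3%, equal loss in both groups, and fatal bleeds being counted from ONS. These are modest shifts. The change is worth making as a cheap improvement in capturing severe primary-outcome events.

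**What to change.** In Outcomes to be measured, Planned use of linked data, and the Phase 2 and Phase 3 Outcomes paragraphs:

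- Count an ONS death with ischaemic stroke or systemic embolism as the underlying cause as a stroke/thromboembolic event on the date of death, if no earlier event is recorded.
- Apply the same rule to ONS bleeding deaths as MB events, so that the fatal limb has a stated source.
- State how a death certified as stroke of unspecified type is classified.
- Add a sensitivity analysis that excludes events known only from the death record.

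The cost is a sentence or two in each place and an ICD-10 list applied to ONS data already requested. The downside is some misclassification of stroke type on death certificates; the rule for unspecified stroke makes its handling explicit, and the sensitivity analysis shows how much the results depend on death-only events.

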**Covariates:**

Covariates believed to potentially confound the relationship between anticoagulation therapy and the outcomes of interest were selected based on previously established associations. These includes age and sex (will be largely accounted for through the matched study design). Stroke risk assessment using CHA2DS2-VASc score and the GARFIELD-AF model, bleeding risk using HAS-BLED and HEMORR2HAGES scores, Charlson comorbidity index, eFI, and IMD.

Concomitant use of medications will also be described in the context of drugs that affect either stroke or bleeding, or commonly interacts with OACs. Such medications would include drug from therapeutic classes of aspirin and other antiplatelets, antihypertensive, statins, antiarrhythmics, diabetic drugs, anticonvulsants, non-steroidal anti-inflammatory drugs, corticosteroids, systemic azoles, HIV protease inhibitors and ciclosporin.

### 3. Phase 3 – Major bleeding events study cohort

**Exposures:**

The exposure of interest will be the occurrence of major bleeding events in the OACs exposed group from the phase two cohort. The exposure will be identified by at least one diagnostic code of a major bleeding event defined specifically according to the ISTH criteria (described in detail in Section D). Read/SNOWMED codes will be used to identify this exposure from patient's primary care electronic records, and hospitalization secondary to bleeding are to be identified through linkage to HES using ICD-10 codes (as listed in Appendix 3).

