**Outcomes:**

The primary outcomes include the reoccurrence of MB events or CRNMB for patients who did or did not continue OACs, the composite of stroke and other thromboembolic events, bleeding or cardiovascular related mortality, and all-cause mortality. Secondary outcome is the prescription of any OACs after the occurrence of the major bleeding events (VKAs or NOACs). We also aim to explore the timing of reinitiating OACs from the indexed bleeding event until the date of OACs prescription, and whether patients have continued on the same OAC before the index haemorrhage event, were switched to another agent after bleeding have occurred (i.e. from warfarin to any NOACs or from any NOACs to warfarin) or received lone antiplatelet therapy.

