score and HAS-BLED score, Charlson comorbidity index, and eFI. In a secondary analysis, we will group patients who resumed OACs according to the type of anticoagulation drug used after the indexed bleeding events and compare the outcomes using Cox models in a similar manner. We will assess the proportional hazards assumption by examining Schoenfeld residuals and confirming that it is not violated. To identify variables independently associated with resuming

OACs after the indexed bleeding event multivariate logistic regression models will be used and fitted with the covariates described in section N. All the statistical analyses will be carried out using STATA (version 16).

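### Phase 3 does not require survival of the index bleed, so patients who die of it are counted as not having resumed anticoagulation

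*Protocol*

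**What the plan says.** The Phase 3 exposure paragraph (Exposures, outcomes and covariates, item 3) takes as its cohort "the occurrence of major bleeding events in the OACs exposed group from the phase two cohort". Entry is by code: "The exposure will be identified by at least one diagnostic code of a major bleeding event defined specifically according to the ISTH criteria". Besides primary care codes, "hospitalization secondary to bleeding are to be identified through linkage to HES using ICD-10 codes". The definition it relies on, under Outcomes to be measured, ends with "and/or (3) fatal bleeding".

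Under Data/statistical analysis, Phase 3, the cohort is split in two by later prescribing: "patients will be divided to 2 groups one for the patients who resumed anticoagulation after the index major bleeding event". Everyone without a later prescription falls in the second group, described as "the other for the group who remained OACs free". Survival time runs from the index bleed to the first of stroke, bleeding or death from any cause. The primary outcomes for the phase include "bleeding or cardiovascular related mortality, and all-cause mortality". A logistic model is then fitted with the stated purpose "To identify variables independently associated with resuming" OACs, using the covariates of section N, which include age, frailty and the anatomical site of the bleed.

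The only remedy for immortal time, a time-varying exposure, is written for Phase 2.

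**The concern.** Resuming an anticoagulant is a decision that only a survivor of the bleed can face. Under the rules as written, a patient admitted with a major bleed who dies of it enters Phase 3, cannot receive a later prescription, and so lands in the group that stayed off treatment. Three results are affected.

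- **Proportion resuming.** The denominator holds people who could not resume, so the figure is too low.
- **Predictors of resumption (aim 6).** Bleeding site, age and frailty plausibly predict death from the bleed. In the logistic model their effect on dying would be read as an effect on prescribing.
- **Outcomes by resumption status (aim 5).** Deaths from the index bleed add early events to the not-resumed arm only, which makes resumption look protective.

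Phase 3 is described under Study type as hypothesis testing, and the Rationale says its results should inform restart decisions. An error with a predictable direction therefore matters.

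**Working it through.** **Step 1: trace the rules.** Fatal bleeding is a major bleed (Outcomes to be measured). Any major bleed with a primary care or HES code admits the patient (Phase 3 Exposures). Anyone without a later prescription is in the group that stayed off OACs (Data/statistical analysis, Phase 3). The same cohort feeds the resumption model. No survivor restriction, landmark or blanking period is stated. Adjusting for time to resumption, and stratifying by restart period (Plan for addressing confounding), do not help, because neither quantity exists for someone who never could restart. The E-value analysis addresses unmeasured confounding, not an entry rule.

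**Step 2: effect on the resumption proportion.** The protocol states no Phase 3 figure to reproduce. Assumed inputs: a fraction *f* of index bleeds is fatal (5%, 15%, 30%), and half of survivors resume.

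- Apparent resumption = 0.5(1 − f)
- Not-resumed group = f + 0.5(1 − f)
- Share of the not-resumed group that died of the index bleed = f / [f + 0.5(1 − f)]

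| f | Apparent resumption | Not resumed | Fatal index bleeds among not resumed |
|---|---|---|---|
| 5% | 0.5 × 0.95 = 47.5% | 52.5% | 0.05/0.525 = 9.5% |
| 15% | 0.5 × 0.85 = 42.5% | 57.5% | 0.15/0.575 = 26.1% |
| 30% | 0.5 × 0.70 = 35.0% | 65.0% | 0.30/0.650 = 46.2% |

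The last column is the share of coded non-resumers for whom no prescribing decision existed.

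**Step 3: crude death comparison.** Assume also that later one-year mortality is 20% in both groups, so that resumption has no effect. Risk in the not-resumed group = [f + 0.5(1 − f) × 0.20] / [f + 0.5(1 − f)].

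- f = 5%: (0.05 + 0.095)/0.525 = 27.6%; ratio 0.20/0.276 = 0.72
- f = 15%: (0.15 + 0.085)/0.575 = 40.9%; ratio 0.49
- f = 30%: (0.30 + 0.070)/0.650 = 56.9%; ratio 0.35

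**Step 4: the planned analysis is a Cox model.** A simulation used the same null scenario, with fatal index bleeds dying on days 1 to 10 and planned resumption on days 14 to 180 (further assumptions). Hazard ratios for resumed versus not:

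| Analysis | f = 5% | f = 15% | f = 30% |
|---|---|---|---|
| Fixed groups, fatal bleeds included | 0.41 | 0.26 | 0.17 |
| Fixed groups, survivors only | about 0.57 | about 0.57 | about 0.57 |
| Time-varying resumption, fatal bleeds included | about 1.0 | about 1.0 | about 1.0 |

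Fatal index bleeds make the fixed-group result worse. Removing them still leaves a ratio near 0.57, because survivors who die before they would have resumed remain classed as not resumed.

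**The case against.** **The survival bias comes mainly from the fixed grouping.** This stands. A reader might infer that the entry rule produces its own survival bias, apart from how resumption time is handled, and that excluding fatal bleeds cures it. Step 4 shows otherwise: time-varying exposure brings the ratio to about 1.0 with fatal bleeds kept, while exclusion alone does not. Time-varying exposure does not repair the resumption proportion or the logistic model, however, because neither uses follow-up time.

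**Counting a death from the bleed as a Phase 3 outcome is not in itself an error.** A reader might infer that aim 5 counts the index bleed as its own consequence. The documents do not support that in general. Aim 5 and Study design speak of outcomes after the bleed, and all-cause mortality counted from the bleed is a legitimate descriptive rate. Deaths on the index day have no follow-up and may drop out of a survival model, depending on software.

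**The absence of a survival condition is not certain.** The study population section is very short in the text at hand, so an exclusion elsewhere cannot be ruled out. The Phase 3 paragraph does not name ONS as a source for the index bleed, so bleeds recorded only on a death certificate may not enter. In-hospital deaths with an HES code still do.

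**A survivor restriction could be left to the SAP.** This carries little weight. The protocol itself fixes the entry rule, the two groups and the time origin, and an SAP that followed them would inherit the problem.

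**Conclusion.** The point holds for the resumption analyses and, in part, for the outcome comparison. As written, patients who die of a coded index bleed are counted as non-resumers. This understates the proportion resuming, confuses determinants of case fatality with determinants of prescribing, and adds early deaths to the not-resumed arm of the fixed-group comparison.

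The direction for the proportion follows from the rules alone. The size does not: case fatality, the share resuming and later mortality are all assumed. With half of survivors resuming, apparent resumption is 47.5%, 42.5% or 35% at fatal shares of 5%, 15% or 30%. The crude ratios in Step 3 should not be read as the bias in the planned Cox models, and the hazard ratios in Step 4 depend on the assumed timing of death and resumption.

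**What to change.** 1. In the Phase 3 Exposures paragraph and in the Phase 3 analysis text, restrict the resumption proportion, the resumption logistic model and the resumed versus not-resumed comparison to patients who survive the index bleed. Survival could be defined as alive at discharge, or alive at a fixed day.
2. Report deaths from the index bleed separately, as case fatality.
3. For aim 5's descriptive rates, keep follow-up from the index bleed and show index-bleed deaths apart from later mortality. Starting all follow-up at discharge would discard in-hospital re-bleeds and strokes and make time zero depend on length of stay.
4. In the Phase 3 Cox models, treat resumption as a time-varying exposure, as the protocol already proposes for Phase 2, or use a landmark.
5. Leave fatal bleeding in the Phase 2 outcome.

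The HES and ONS linkages needed are already requested. The cost is a change of wording and of the Cox specification, a somewhat smaller cohort for the resumption analyses, and resumption results that apply to survivors of the index bleed, who are the patients facing the decision.
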